# A community-based cluster randomised controlled trial in rural Bangladesh to evaluate the impact of the use of iron-folic acid supplements early in pregnancy on the risk of neonatal mortality: the Shonjibon trial

**DOI:** 10.1186/s12889-018-5713-1

**Published:** 2018-07-03

## Abstract

**Background:**

Iron-deficiency is the most common nutritional deficiency globally. Due to the high iron requirements for pregnancy, it is highly prevalent and severe in pregnant women. There is strong evidence that maternal iron deficiency anaemia increases the risk of adverse perinatal outcomes. However, most of the evidence is from observational epidemiological studies except for a very few randomised controlled trials. IFA supplements have also been found to reduce the preterm delivery rate and neonatal mortality attributable to prematurity and birth asphyxia. These results combined indicate that IFA supplements in populations of iron-deficient pregnant women could lead to a decrease in the number of neonatal deaths mediated by reduced rates of preterm delivery. In this paper, we describe the protocol of a community-based cluster randomised controlled trial that aims to evaluate the impact of maternal antenatal IFA supplements on perinatal outcomes.

**Methods/design:**

The effect of the early use of iron-folic acid supplements on neonatal mortality will be examined using a community based, cluster randomised controlled trial in five districts with 30,000 live births. In intervention clusters trained BRAC village volunteers will identify pregnant women & provide iron-folic acid supplements. Groundwater iron levels will be measured in all study households using a validated test kit. The analysis will follow the intention to treat principle. We will compare neonatal mortality rates & their 95% confidence intervals adjusted for clustering between treatment groups in each groundwater iron-level group. Cox proportional hazards mixed models will be used for mortality outcomes & will include groundwater iron level as an interaction term in the mortality model.

**Discussion:**

This paper aims to describe the study protocol of a community based randomised controlled trial evaluating the impact of the use of iron-folic acid supplements early in pregnancy on the risk of neonatal mortality. This study is critical because it will determine if antenatal IFA supplements commenced in the first trimester of pregnancy, rather than later, will significantly reduce neonatal deaths in the first month of life, and if this approach is cost-effective.

**Trial registration:**

This trial has been registered with the Australian New Zealand Clinical Trials Registry (ANZCTR) on 31 May 2012. The registration ID is ACTRN12612000588897.

## Background

Globally, 2.6 million children died in the neonatal period, the first 28 days of life in 2016 [1]. Over the last two decades, there has been a substantial global reduction in under-5 child mortality rates. Compared to that, the reductions in neonatal deaths have been slower. Neonatal deaths accounted for 46% of all under-five deaths in 2016 compared with 37·4% in 1990 [1, 2]. Effective interventions directed specifically at preventing neonatal deaths are required to improve overall child survival.

A systematic review in 2005 found that up to 70% of neonatal deaths, worldwide, could be averted by implementing sixteen evidence-based interventions at near universal coverage (99%) that incorporated preconception, antenatal, intrapartum and postnatal interventions [3]. However, this review did not include antenatal iron and folic acid (IFA) supplementation for pregnant women. At that time no trials had reported the effects of IFA on neonatal mortality, although these supplements were known to benefit both maternal and infant health [3].

Iron-deficiency is the most common nutritional deficiency globally. Due to the high iron requirements for pregnancy, it is highly prevalent and severe in pregnant women [4]. In Bangladesh, 42% of all women of reproductive age and nearly 50% of pregnant women had anaemia in 2011 [5]. However, the prevalence of iron deficiency was lower. The first national micronutrients status survey, published in early 2013, reported that iron deficiency among non-pregnant non-lactating women was 7.1%. The ferritin level was significantly higher in areas where groundwater iron concentration was high. The survey findings also suggest a positive association between natural iron content in groundwater and iron status of women [6].

There is strong evidence that maternal iron deficiency anaemia increases the risk of adverse perinatal outcomes. However, most of the evidence is from observational epidemiological studies except for a very few randomised controlled trials. A community-based cluster randomised trial from China reported a 54% reduction of early neonatal mortality in newborns of women who received IFA supplements compared to those receiving folic acid alone (HR 0.46, 95%CI: 0.21–0.98) [7]. Secondary analyses of this trial found a 71% reduction in neonatal mortality in women who started IFA supplements in the first trimester of pregnancy (HR 0.29, 95%CI: 0.09–0.88) [8]. A meta-analysis of prospective observational studies, reported reductions in perinatal mortality (stillbirth and early neonatal mortality) with each 1 g/dl increase in the population mean haemoglobin (RR 0.72, 95%CI: 0.65–0.81) [9]. A pooled analysis of data from Indonesian Demographic and Health Surveys, which included 40,576 singleton live-born infants, found mothers using any IFA supplements during pregnancy significantly reduced the risk of early neonatal death of their newborns after adjustment for potential confounders [10]. Similarly, a pooled analysis from Pakistan on 8512 live births reported maternal antenatal IFA supplements significantly reduced the adjusted risk of death on day 0 by 33% and during the neonatal period by 29%. Initiating IFA supplements in the first four months of pregnancy, significantly reduced the adjusted risk of neonatal mortality by 35% [11].

IFA supplements have also been found to reduce the preterm delivery rate and neonatal mortality attributable to prematurity and birth asphyxia [7]. Other studies from low-income countries have reported that preterm delivery is one of the main contributors to neonatal deaths [12, 13]. These results combined indicate that IFA supplements in populations of iron-deficient pregnant women could lead to a decrease in the number of neonatal deaths mediated by reduced rates of preterm delivery. We thus propose a large-scale prospective trial to measure the impact of the early introduction of antenatal iron/folic acid supplementation in pregnancy on neonatal outcomes in rural Bangladesh. We will employ a community-based, cluster randomized controlled trial design, in which pregnant women will be randomly allocated to the enhanced iron/folic acid distribution program, or to the current usual programs. We have chosen the current usual programs as our comparator. We didn’t consider placebo because WHO and Government of Bangladesh have a recommendation that pregnant women should receive 60 mg of iron supplementation. But the implementation of this recommendation is inadequate. Surveys indicate that only 52% of rural women reported any use of iron/folic acid in their last pregnancy but this dropped to 39% for the poorest households, and to 34% for women with no education (3). Also, the median gestation when women start antenatal care (and would have access to iron/folic acid supplements) is 5.2 months (3) .

### Objectives and hypothesis

The trial objectives are to evaluate the effect of early availability and promotion of IFA supplements on neonatal mortality, low birthweight and preterm delivery. The primary hypothesis is that in a community-based, cluster randomized controlled trial of women from rural Bangladesh, daily supplementation with 60 mg elemental iron and 400 μg folic acid starting in the first trimester of pregnancy, and sustained for at least 180 days, will reduce neonatal mortality by 25% from 33/1000 to 24.8/1000 live births compared to usual iron-folic acid supplementation programs.

The secondary hypotheses are that the early availability and promotion of IFA supplements in intervention clusters will reduce preterm delivery by 30% (15% in control to 10.5% in intervention), and low birth weight by 30% (15% in control to 10.5% in intervention). We further hypothesised that household wealth and maternal education would modify the neonatal mortality responses with a greater reduction for women from the poorest households, and women with no education. We also hypothesised that the early start to IFA supplements would not increase iron-related side effects, e.g. nausea & vomiting in intervention clusters and will be cost-effective in reducing neonatal mortality in intervention clusters.

## Methods

### Study design

This study is a cluster randomised controlled trial, with 2-arm parallel groups, superiority design and 1:1 allocation ratio. The cohort of the mother-child dyads will be followed up from recruitment until 42 days after birth.

### Study setting

We will conduct the Shonjibon trial in five districts in Dhaka Division, Bangladesh. These districts are Netrokona, Kishoreganj, Mymensingh, Sherpur, and Gazipur, with a total number of 47 Upazila (subdistricts) and a combined population of 20 million. Our study implementing partner BRAC, a non-government organisation co-ordinates a community-based maternal, neonatal and child health program in the area which includes a prospective pregnancy surveillance and home-based antenatal care program. The Shonjibon study area will consist of 24 Upazilas from these five districts (Fig. 1). We will exclude five Upazilas from Kishoreganj, six Upazilas from Netrokona and two Upazilas from Sherpur because of insufficient BRAC Program Officer (PO) coverage. We will also exclude three Upazilas from Gazipur because of the high number of garment industries, which would have high numbers of working women and would be difficult to follow-up and eight Upazilas from Mymensingh because of the high prevalence of malaria and kalazar.

**Fig. 1 Fig1:**
[figure not shown]
Map of study area, Shonjibon Trial (created by the authors)

### Cluster selection

We will define a cluster as a BRAC PO area, which will consist of a pair of BRAC village field workers (called Shasthya Kormi or SK) and their 20 BRAC village volunteers (referred to as Shasthya Shebika or SS) who are supervised by a single BRAC PO. A BRAC PO area approximately comprises of 40 to 50 villages with an average population of 13,000 people. We will have a total number of 112 BRAC PO for randomisation. We will randomly select 100 clusters with an equal number of clusters in each arm. The research team took written approval for the study from Directorate General of Health Service (DGHS) under Ministry of Health & Family Welfare before allocating the clusters to a treatment group or the trial interventions begin.

### Eligibility criteria for inclusion of cluster

We will exclude any potential BRAC PO area (cluster) if there are any other maternal and or neonatal interventions either by the government or non-government organisations in the area. We will identify any such program by contacting local officials in the sub-districts in the Dhaka Division. We will exclude areas where access is extremely difficult, for example in flood-prone areas. All women aged between 15 to 49 years, who are pregnant and their gestational age is ≤90 days, and are permanent residents of the Shonjibon study area will be eligible for the study.

#### Formative research

Before the intervention started, we conducted a formative study using qualitative methods. We collected the data from July to October 2012, in two villages, one in Mymensingh and one in Netrokona – two of the five districts included in the Shonjibon Trial. The field team consisted of three women and two men trained in anthropology or social sciences, who had experience in collecting qualitative data. Four qualitative methods – in-depth interviews (35 pregnant women, 20 older women and 11 husbands), key informant interviews (20 with CHWs, program managers, informal care providers, gynaecologists and traditional birth attendants), focus group discussions (2 with Shasthya Shebika and 1 with female college students) and observations of the lowest level of health facility (community clinics) (2) were conducted. We explore women’s and family members’ perceptions of: cultural norms during pregnancy; birth weight; IFA supplementation; and experience using IFA supplements during pregnancy. We conducted the key informant interviews to understand the community norms around IFA supplementation, and challenges and successes of the existing programme. We used FGDs to understand both perceptions regarding the need for IFA tablets during pregnancy and the state of IFA supplementation programmes. In two community clinics, we conducted an hour-long observation to understand the implementation of the national IFA programme.

#### Intervention

From the formative study, we identified culturally appropriate and feasible ways of implementing the intervention [14]. The findings of the formative study suggested that introduction of IFA supplements early in pregnancy is feasible with support from BRAC or government community health workers. The formative study also suggested to include culturally sensitive reasons for the use of IFA supplements during pregnancy, improvement of the community health-worker training modules and to standardise messages across all health workers. We conducted a pilot study in four BRAC village fieldworker areas, two with intervention and two comparison areas, to test the feasibility of our intervention.

### Early identification of pregnancy

In the intervention clusters, trained SS will identify pregnant women through systematic door-to-door visits of the households in her catchment area and follow-up with all women of reproductive age about their recent history of missed menstrual periods. We will financially incentivise the SS for early identification of pregnant women.

### Regular supply of IFA supplements and counselling

Upon receiving the consent icddr,b study staff (Field Implementers or FI) will hand over the first two months of supply of iron-folic acid capsules, each containing 60 mg of elemental iron and 400μg of folic acid. She will also counsel the mother about the benefits of IFA supplements in pregnancy. The SS will then make regular fortnightly visits to the woman until delivery to ensure resupply of supplements, and provide counselling in support of early uptake, continued use, and compliance with the supplementation regime until delivery. This intervention is consistent with the Bangladesh Ministry of Health guidelines.

### Improve adherence and monitor compliance

To improve adherence, a local pharmaceutical company (Eskayef Bangladesh Limited) will produce IFA supplements in an attractive capsule shell and special blister package. Each strip will consist of 15 capsules. At the time of enrolment, we will assign each mother a box consisting of 8 months of supply of iron-folic acid supplements. We will attach the details of the pregnant women to the box during registration in the trial. At the time of resupply, the SS will collect the empty strips from the previous round. If she finds any unused capsules, she will inquire about the missing doses and further counsel the women about the importance of regular consumption of IFA supplements. We will provide a specially designed medicine box to each participant to preserve the medicine. It will also serve as a reminder for regular consumption and safely store the medicines away from child access. In addition to this, a special call centre will be set up centrally where trained nutrition counsellors will systematically make bi-weekly calls to monitor compliance with the supplementation regime.

### Concomitant treatment

The research team will advise all Shonjibon study participants in the intervention arm not to consume any additional iron or folic acid supplements from other sources during her pregnancy.

### Management and training

Overall around 3920 SS and 100 FI will deliver the intervention, under the supervision of central field supervisory team. There will be one FI for each cluster. The central team will comprise of three research fellows, one medical officer and one research investigator and one BRAC national manager. The field supervision team will comprise of five Field Research Officers and five District Managers. We will train the BRAC village workers and volunteers in sub-district health centres to detect and monitor pregnancies, to maintain pregnancy records, to manage supply and distribution of supplements, communication and counselling skills for behaviour change related to use of iron-folic acid supplements. The central team will train the field team and monitor the process of delivery of the intervention. The BRAC PO will provide technical support to the SK and SS, and will help them resolve any problems through regular meetings in the field.

#### Control

We used usual iron supplementation program as the comparator. We will identify and confirm pregnant women in the control clusters using methods similar to those described for the intervention arm. Women will not receive any additional information or counselling other than usual standard care provided by the existing BRAC structure. Both intervention and control treatment arms will receive the usual antenatal and postnatal care services by BRAC.

#### Trial outcomes

The primary trial outcome will be the difference in the neonatal mortality rate between the intervention and control areas. The secondary trial outcomes will include: (1) percentage of women using IFA supplements in the first trimester of pregnancy; (2) percentage of live births with low birth weight and with preterm delivery; (3) percentage of neonatal deaths attributable to preterm delivery, and to birth asphyxia; (4) mean marginal additional expenditure associated with early IFA supplements, and the mean cost per neonatal death prevented; (5) the percentage of pregnant women reporting side effects including nausea and vomiting.

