### Statistical analysis

Data analysis will be by intention to treat. We will conduct analyses at the infant level adjusted for the cluster randomisation. The primary analyses will compare the neonatal mortality rates and their 95% confidence intervals adjusted for clustering and groundwater iron level in each group. Secondary analyses will examine each outcome variable using separate mixed models. We will use Cox proportional hazards mixed models for mortality outcomes and include groundwater iron level as an interaction term in the mortality model. We will use population average Poisson model for other outcomes including preterm, small for gestation and low birth weights. Models will include treatment group as a fixed effect, community-cluster as a random effect to account for the cluster effect. The models will evaluate the impact of the interventions over time by testing for an interaction between time and intervention group. We will conduct analyses to identify the subgroups (based on household wealth, sex of infant and maternal education) that modify the response to the intervention. We will check the model assumptions and make appropriate adjustments to the analysis where necessary. Descriptive analysis will be performed to present the cause of death. We will compare the causes of death by sex of newborn, the time-period of death, and treatment arms (intervention Vs control). χ^2^ test or Fisher’s Exact test after adjusting for cluster effect will be used when appropriate. The economic analysis will estimate the incremental cost per life saved per year of the intervention over standard care. We will use sensitivity analyses of the findings to assess uncertainty in key parameters. Stata V.14 (StataCorp. 2015. Stata Statistical Software: Release 14. College Station, TX: Stata Corp LP.) will be used for all analyses.

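### Secondary outcome 3 measures preterm and asphyxia deaths as a share of neonatal deaths, which need not move with the number of those deaths per live birth

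*Protocol article*

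**What the plan says.** The Trial outcomes section lists five secondary outcomes. The third is the "percentage of neonatal deaths attributable to preterm delivery, and to birth asphyxia", so its denominator is neonatal deaths. The item just before it uses births as the denominator: "percentage of live births with low birth weight and with preterm delivery". The primary outcome covers all causes together: "The primary trial outcome will be the difference in the neonatal mortality rate between the intervention and control areas".

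The Statistical analysis section introduces the cause-of-death work with "Descriptive analysis will be performed to present the cause of death". It then goes further: "We will compare the causes of death by sex of newborn, the time-period of death, and treatment arms", for which a χ² "test or Fisher’s Exact test after adjusting for cluster effect will be used when appropriate". Cox mixed models are planned for mortality outcomes in general, but the article names no cause-specific rate or hazard.

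The Background argues from counts of deaths. It cites evidence that supplements lowered neonatal mortality from prematurity and asphyxia, and concludes that supplementation "could lead to a decrease in the number of neonatal deaths mediated by reduced rates of preterm delivery".

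**The concern.** The Background's question is whether fewer live-born infants die of prematurity or asphyxia. Outcome 3 answers a different one: among infants who died, what fraction died of those causes. Death is itself the primary endpoint and occurs after randomisation, so the two groups of deaths being compared are selected by an event that the intervention is designed to change.

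The share in an arm is the cause-specific rate divided by the all-cause rate. An effect on both can cancel, and an effect on the denominator alone can move the share. A flat share could then be read as no effect on preterm or asphyxia deaths when they had fallen. A rising share, with a small p-value attached, could be reported when they had not changed. This follows from carrying out the outcome as it is written; it does not come from detail left to a fuller document.

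**Working it through.** The article states no figure for outcome 3, so there is none to reproduce. The check asks how the share behaves under the trial's own planning rates.

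**Inputs**
- Neonatal mortality of 33 (control) and 24.8 (intervention) per 1000 live births: Sampling frame and sample size.
- 30,000 live births allocated 1:1, so 15,000 per arm: same section.
- Control share of deaths due to the target cause: not given. Assumed 30%, 50% and 70%. The argument applies to each cause separately or to the two combined.

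**Expected deaths.** 15,000 × 0.033 = 495 in control; 15,000 × 0.0248 = 372 in intervention.

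**Relation between share and rate.** Target-cause rate = share × all-cause rate. Hence

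share (intervention) / share (control) = target-cause rate ratio / all-cause rate ratio.

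The share falls only if the target causes fall by proportionally more than deaths as a whole. The all-cause rate ratio planned here is 24.8/33 = 0.752.

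**Scenario A: every cause falls in proportion.** The share is the same in both arms whatever its value.

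| Control share | Target rate per 1000, control → intervention | Rate ratio | Intervention share |
|---|---|---|---|
| 30% | 9.9 → 7.44 | 0.752 | 30% |
| 50% | 16.5 → 12.4 | 0.752 | 50% |
| 70% | 23.1 → 17.36 | 0.752 | 70% |

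**Scenario B: target-cause deaths do not change and the whole fall of 33 − 24.8 = 8.2 per 1000 is in other causes.** Rate ratio 1.00.

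| Control share | Target rate per 1000, both arms | Intervention share |
|---|---|---|
| 30% | 9.9 | 9.9/24.8 = 39.9% |
| 50% | 16.5 | 16.5/24.8 = 66.5% |
| 70% | 23.1 | 23.1/24.8 = 93.1% |

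With an exact 25% fall (24.75 per 1000), the first two shares are 40.0% and 66.7%. A two-proportion test on 495 and 372 deaths, ignoring clustering, would have about 86% power to declare this difference at a 30% control share and over 99% at 50% or 70%.

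**Scenario C: the whole fall of 8.2 per 1000 is in the target causes.**

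| Control share | Target rate per 1000, control → intervention | Intervention share |
|---|---|---|
| 30% | 9.9 → 1.7 | 1.7/24.8 = 6.9% |
| 50% | 16.5 → 8.3 | 8.3/24.8 = 33.5% |
| 70% | 23.1 → 14.9 | 14.9/24.8 = 60.1% |

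Here the share moves in the right direction.

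**Scenario D: target causes fall 20% and other causes 40%, control share 50%.** Target 16.5 × 0.8 = 13.2; other 16.5 × 0.6 = 9.9; total 23.1. The share rises from 50% to 13.2/23.1 = 57.1% although target-cause deaths fell (rate ratio 0.80).

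The rate per live birth gives the right answer in all four scenarios. The share does so only in C.

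**The case against.** The strongest reply is that the trial will report all-cause neonatal mortality by arm, so anyone can multiply it by the share and recover the cause-specific rate. The plural reference to mortality outcomes under the Cox models does not exclude cause-specific death, and the full analysis plan, which is not shown, may specify it. This answers a stronger inference that a reader might draw, namely that the trial cannot show whether these deaths fell. The data can show it. What remains is that the outcome as defined, and the comparison tied to it, use the share.

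The article also calls the cause-of-death analysis descriptive. That counts in its favour, but the next sentences add a comparison by arm with significance tests, and the share is listed as a trial outcome.

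A further reply is that outcome 3 is not the main test of the mechanism. That is right. Preterm delivery among live births is in outcome 2, with its own hypothesis and sample size, while the Objectives and hypothesis section states no hypothesis on cause-specific mortality. It would go too far to say that the mechanistic case rests on outcome 3.

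Scenario C is also the one nearest to the trial's rationale, and there the share behaves well. Scenario B at a 30% share needs other-cause deaths to fall from 23.1 to 14.9 per 1000, about 36%, with no effect on the target cause. The documents do not make that likely, and a reader who also saw total mortality down by a quarter would hardly infer harm. Scenario A needs no such assumption: it only spreads the planned reduction evenly over causes.

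Finally, one might say that the comparison departs from intention to treat. That is imprecise. Deaths are still grouped by allocated arm; the difficulty is conditioning on an event after randomisation.

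**Conclusion.** The point holds for one secondary outcome. Outcome 3 fixes a denominator that the intervention is meant to change, and the planned between-arm comparison therefore does not test whether preterm or asphyxia deaths fell. Under an even 25% reduction the share is unchanged while target-cause deaths fall by a quarter; this holds at any control share. If only other causes fall, the share rises from 30% to 40% or from 50% to about 67% with target-cause deaths unchanged. The sizes in that second case depend on the assumed control shares; the direction does not. The quoted power figures ignore clustering.

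The primary outcome and its analysis are not affected, and the cause-specific rate can be recovered from data the trial already plans to hold. It is worth correcting because the change is nearly free and removes a result that could be flat or reversed when these deaths fall.

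**What to change.** Define outcome 3 as neonatal deaths attributable to preterm delivery, and separately to birth asphyxia, per 1000 live births in each arm, with all live births as the denominator. Estimate the effect as a cluster-adjusted rate ratio, or as a cause-specific hazard ratio from the mixed models already planned for mortality outcomes. Keep the percentage of deaths by cause as a descriptive table, without a test between arms.

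The cost is a change of wording in the outcome list and the analysis section. Live births, deaths and verbal autopsy causes are already collected. The price is fewer events per cause, and so wider intervals. At a 30% control share under scenario A, about 495 × 0.30 = 148.5 and 372 × 0.30 = 111.6 deaths are expected, roughly three per control cluster (148.5/50). Power to detect the rate ratio of 0.752 is then about 63% before any allowance for clustering, against 85% at a 50% share and 94% at 70%. The result should be presented as an estimate with its interval.
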